#### 2.6.2. Secondary Outcome Measures

In order to obtain efficacy data, given the heterogeneity of the clinical population in terms of both chronological age and functional profile, a wide set of tests with normative data covering an extended age range have been defined. This approach will allow the selection of the tests most suited to each patient’s functional profile for the pre–post-training assessment of different cognitive, neuropsychological, motor, and language abilities, as detailed in Table S2. Moreover, the training’s impact on daily life functioning will be considered.

Specifically, the following outcome measures, grouped considering the function assessed, will be deemed.

Attention: assessment of visual sustained and selective attention through different barrage tasks of increasing complexity (i.e., Leiter-3—Sustained attention subtest [41], BIA—CP subtest [53]);Visuomotor processing: assessment of the ability to integrate and coordinate visuo-perceptual and motor functions by coping geometrical figures or following a narrow path under time pressure (i.e., NEPSY II—Visuomotor precision subtest [54], VMI [55], TPV test [56]);Visuospatial processing: assessment of the ability to be oriented in visuospatial coordinates by judging lines’ orientation or locating a target on a map (i.e., NEPSY II—Arrow subtest, NEPSY II—Route finding subtest [54]);Working memory: assessment of the ability to recall and/or actively manipulate visuospatial and verbal information through the repetition of a sequence of targets in the same or reverse order (i.e., BVN—Digit Span [57,58]; BVS Corsi—Corsi block tapping test [59]);Daily life functioning: assessment of clinical behavior and executive functioning in daily life contexts and activities (i.e., CPRS [60], BRIEF—P and 2 versions [61,62]);Learning skills: assessment of reading and writing abilities, considering different tasks of increasing length and complexity (i.e., DDE 2—reading and writing subtests [63], MT-3 [64], Martini [65], BVSCO 2—text writing subtests [66]);Receptive language: assessment of grammar and vocabulary comprehension, using multiple-choice figurative tasks (i.e., PPVT-R [67], TCGB [68]);Walking: assessment of aerobic capacity and endurance by walking task (i.e., 6MWT [69]);Gross-motor function: assessment of gross-motor functions and praxis skills, considering performances in different areas (i.e., GMFM- 88 [70], MABC-2 [71], APCM-2 [72]);Static and dynamic balance: assessment of functional balance skills through a set of different tasks (i.e., PBS [73], FRT [74], TUG [75]);Upper limb: assessment of upper limb motor abilities through unimanual and bimanual tasks, but also considering daily life activities (i.e., BoHA [76], AHA [77], MA2 [78], BBT [79], ABILHAND-Kids [80]);Movement disorders: assessment of movement disorder and their impact on motor functions and daily life activities, considering different body regions at rest and while performing specific tasks (i.e., MD-CRS 4-18 R [81]).

Furthermore, treatment effectiveness will be examined using the Goal Attainment Scale (GAS) [82], a rehabilitation outcome measure, which is scored based on individual goals hypothesized and achieved throughout the intervention. Finally, the merging of these datasets together with primary outcome measures will contribute to the formulation of innovative organizational models, incorporating tele-assistance and tele-rehabilitation pathways.

The primary and secondary outcome measures will be acquired and collected through electronic Case Report Forms that collect data coming from both the online questionnaires on acceptability and usability and data on the performances (see the secondary endpoints) of the involved children collected and filled-in the eCRF by the healthcare professionals.

### 2.7. Statistical Analyses

Descriptive statistics (means, standard deviation, frequencies) will be investigated, analyzing potential baseline differences between groups explored and computing the p values. The normal distribution of the sample will be investigated through the Shapiro–Wilk test. Subsequently, a comprehensive analysis, both qualitatively and quantitatively, will be conducted on the questionnaire data gathered from various stakeholders, aiming to assess the usability and acceptability of the devices used. Statistical analysis, such as ANOVA or regression, will be carried out to determine differences based on age, diagnosis, functional profile (cognitive and motor outcomes), and devices used during tele-rehabilitation. Furthermore, inferential analyses will be carried out to assess pre–post-treatment differences, gain efficacy data, and also consider the different devices used during tele-rehabilitation pathways. Finally, flowchart diagrams will be created to illustrate the different organizational models identified. Statistical significance will be considered at p<.05. Statistical Package for Social Sciences (SPSS) (IBM Statistic) will be adopted for carrying out the statistical analyses.

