#### 2.1.2. Phase II

During this phase, the validation of the implemented technologies will be conducted through a wait-list study (Figure 3) with two parallel arms. One hundred subjects (comprising 80 children and 20 young adults) will be recruited from the aforementioned clinical centers. The wait-list design study will ensure that all enrolled patients will be eligible for the experimental treatment, thus avoiding issues related to equipoise.

After the identification of eligible subjects according to inclusion and exclusion criteria (described below), participants will be stratified according to several criteria, including (i) diagnosis (congenital or acquired developmental disorder group), (ii) gross motor function classification system (GMFCS) level (GMFCS I–II/GMFCS III–IV), (iii) age group (6–10/11–15/16–20/21–30), (iv) and technology utilized (APP vs. Home Kit). Then, participants will be randomly assigned to the experimental group (EG)—receiving a 3-month tele-rehabilitation immediately—or the wait-list group (WG)—continuing traditional rehabilitation care for the same duration. All subjects will be evaluated before (T0) and after (T1) the 3-month intervention period (tele-rehabilitation or traditional rehabilitation), using standardized clinical tests. Moreover, participants enrolled in the WG will be re-evaluated at the end of the 3 months of tele-rehabilitation training (T1 plus). Finally, at the end of tele-rehabilitation training, ad-hoc questionnaires will be administered to the main stakeholders to assess the systems’ usability and acceptability. The program of enrolment, interventions and assessments designed according to SPIRIT guidelines are shown in Figure 4.

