#### 2.1.3. Phase III

The third and final phase will involve the analysis of usability and acceptability data, considering the feasibility measures acquired. Moreover, efficacy data acquired from pre–post-intervention cognitive, motor, and language assessments will be considered. Furthermore, the research group will perform interviews with patients and parents to collect information regarding unmet needs in relation to the patient’s pathway. The healthcare professionals will be involved in a Focus Group to analyze the strengths and weaknesses of organizational models with and without technology. The interviews with patients and caregivers will be one-on-one and face-to-face. The interviews will be performed online. The interview will follow a semi-structured questionnaire that the research group will develop for the project. The Focus Group is a qualitative methodology based on discussion among participants managed by a moderator. The Focus Group with healthcare professionals will conduct in presence in groups of up to 12 participants. It is planned to carry out two Focus Groups, one with professionals from the Azienda USL Toscana Nord Ovest and one with professionals from the IRCCS Stella Maris. The obtained results will allow the definition of innovative organizational models, including tele-assistance and tele-rehabilitation pathways, to be validated and thus integrated into the planning of the Regional Health Service (SSR).

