### 2.6. Outcome Measures

#### 2.6.1. Primary Outcome Measures

The acceptability and usability of ICT technologies in pediatric populations will also be assessed through the following Key Performance Indicators (KPIs), summarized in Table S1.

Service and technology KPIs:Study adherence: rate of acceptance of the participation in the study calculated as the number of eligible participants that agree to join the project;Adherence to training: total number of training sessions completed on the total number of sessions scheduled by the clinicians;Number of dropouts: number of participants that will not complete all of the study procedures;Number of sessions completed in the target time: total number of training sessions completed in the timeframe set by clinicians;Hardware and software technical problems: number of issues and malfunctioning experiments during the training sessions;Ad hoc feasibility questionnaires: according to the standard definitions of usability [49,50,51] and acceptability [52], specific items ranked on a five-point Likert scale (1 most negative, 5 most positive) will be defined. The aim will be to investigate four feasibility domains: (i) exercise customization, (ii) adaptability of home training, (iii) required effort and (iv) systems suitability. An introductory section will include both open and multiple-choice questions to collect information about the patient, the experimenter who fills out the questionnaire, and the devices and peripherals used. Three questionnaire versions will be available for different stakeholders (participants, parents, clinicians). The children’s format will be structured to be easy to understand for even the youngest participant and facial expressions shown through emoticons will help the children to assign the Likert-scale rank. Questionnaires will, therefore, be filled out at the end of the training by clinicians who administered the session, parents and participants over 6 years old and with cognitive and neuropsychological functioning, allowing full question comprehension and adequate cooperation;Medical Equipment Utilization: for each involved technology: the average time of utilization per session; the related consumables (if any)—the related power consumption;Set-up time: the time necessary for setting up the involved technologies;Training time/learning curve (for patients).

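### For clinician-completed usability questionnaires, the named ANOVA or regression carries no clinician effect, so error rates may be wrong in either direction where clinicians rate several patients

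*Protocol article*

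**What the plan says.** Section 2.6.1 (Primary Outcome Measures) lists ad hoc feasibility questionnaires among the primary measures, in separate versions for participants, parents and clinicians. On the clinician version: "Questionnaires will, therefore, be filled out at the end of the training by clinicians who administered the session". An introductory section serves "to collect information about the patient, the experimenter who fills out the questionnaire, and the devices and peripherals used". The clinician form is therefore tied to one patient and carries the rater's identity.

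Section 2.1.2 (Phase II) sets the number of patients: "One hundred subjects (comprising 80 children and 20 young adults) will be recruited from the aforementioned clinical centers". Both arms eventually receive tele-rehabilitation, so up to about 100 patients can have a clinician form.

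Section 2.7 (Statistical Analyses) covers the questionnaire data from all stakeholders: "Statistical analysis, such as ANOVA or regression, will be carried out to determine differences based on age, diagnosis, functional profile". The same sentence adds the devices used, and significance is set at p<.05. It names no clinician term, mixed model or clustered standard error.

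The number of clinicians is not given. The nearest figure is in section 2.1.3 (Phase III), which plans two Focus Groups of professionals, one per institution, each "in groups of up to 12 participants".

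**The concern.** If one clinician rates several patients, that clinician's general leniency or strictness enters all of those scores, and they are not independent. An ordinary ANOVA or regression computes its standard errors as if they were.

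The tested factors are not protected by randomization. Device is a stratification factor fixed before allocation, and diagnosis, age and profile are patient attributes. If a clinician works mainly with one device or one diagnostic group, for example because of institution or specialty, a difference between raters can look like a difference between devices or diagnoses. If a factor is spread evenly within clinicians, the opposite happens: rater variation stays in the residual and the test loses power.

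Rater differences are plausible on the article's own account, since the Discussion describes apprehension and resistance to these technologies among health professionals. Section 2.6.2 says the primary outcome data will feed the organizational models, so a spurious device or diagnosis difference could be carried into them.

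**Working it through.** The plan gives no figure for this analysis, so there is none to reproduce. The sample-size statement in section 2.3 concerns a two-group *t*-test and does not enter here.

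**Inputs from the document.** 100 patients (section 2.1.2); one clinician form per patient, inferred from the content of the form (section 2.6.1); significance level 0.05 (section 2.7; sidedness not stated, two-sided used).

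**Inputs assumed.** 6, 10, 20 or 24 clinicians; ICC from 0 to 0.3; four ways in which a two-level factor may be spread over clinicians. The upper value of 24 is 2 × 12, the most professionals the two Focus Groups could hold. It is a plausible figure for raters, not a documented one. At 24 clinicians the average load is 100/24 ≈ 4.2 patients each.

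**Formulas.** With m patients per clinician and a factor constant within clinician, the variance of the group difference is inflated by the design effect DE = 1 + (m − 1) × ICC. The naive rejection rate is then roughly 2[1 − Φ(1.96/√DE)]. For 10 clinicians and ICC 0.1, DE = 1 + 9 × 0.1 = 1.9, 1.96/√1.9 = 1.42, and the rate is about 15.5%. With the factor balanced within clinician, only the residual part (1 − ICC) contributes, and the rate is roughly 2[1 − Φ(1.96/√(1 − ICC))]. For ICC 0.3, 1.96/√0.7 = 2.34, and the rate is about 1.9%.

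**Simulation.** 20,000 runs per setting, no true factor effect, total variance 1, two-group *t*-test ignoring clinician. Equal clusters give 96 forms with 6 or 24 clinicians and 100 with 10 or 20. In the 80/20 setting, half the clinicians use one factor level with probability 0.8 and the other half with probability 0.2.

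| Clinicians (patients each) | ICC | DE | Constant within clinician | 80/20 | Unrelated to clinician | Balanced within clinician |
|---|---|---|---|---|---|---|
| 6 (16) | 0.05 | 1.75 | 13.9% | 8.4% | 4.9% | 4.5% |
| 6 (16) | 0.1 | 2.5 | 22.5% | 11.4% | 5.2% | 4.1% |
| 6 (16) | 0.3 | 5.5 | 42.7% | 23.8% | 5.1% | 2.5% |
| 10 (10) | 0.05 | 1.45 | 10.8% | 6.9% | 5.1% | 4.5% |
| 10 (10) | 0.1 | 1.9 | 15.4% | 8.7% | 5.1% | 4.1% |
| 10 (10) | 0.3 | 3.7 | 31.7% | 16.7% | 5.1% | 2.2% |
| 20 (5) | 0.05 | 1.2 | 7.5% | 5.8% | 5.0% | 4.7% |
| 20 (5) | 0.1 | 1.4 | 10.1% | 6.5% | 5.0% | 3.7% |
| 20 (5) | 0.3 | 2.2 | 18.9% | 9.9% | 4.8% | 2.0% |
| 24 (4) | 0.05 | 1.15 | 6.6% | 5.5% | 5.1% | 4.4% |
| 24 (4) | 0.1 | 1.3 | 8.6% | 6.3% | 5.2% | 3.9% |
| 24 (4) | 0.3 | 1.9 | 15.7% | 9.0% | 5.0% | 2.2% |

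With ICC 0 every setting gives about 5% (4.7% to 5.5%). The simulated 15.4% and 2.0% to 2.5% agree with the two hand calculations.

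**The case against.** The strongest reply is that section 2.7 does not fix an analysis that ignores clinician. It offers ANOVA and regression as examples, and a regression with a clinician term would fit the wording. The form records who filled it in, and the fuller protocol or analysis plan may specify the model. This stands, in that the article cannot be said to have ruled out a clinician effect. What remains is that the only methods named for a primary measure assume independent scores in their ordinary form.

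A reader might infer that a small, known group of clinicians does all the rating. The documents do not support that. No count of clinicians or of patients per clinician is given, and the Focus Group limit is a discussion-group size that does not bound the raters. Some repeat rating is nevertheless very probable, because avoiding it would take about 100 different clinicians at two institutions. If several clinicians rated the same patient, that would add dependence, not remove it.

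A reader might also infer that device or diagnosis effects will be declared far too often. That is not supported either. Inflation needs positive ICC, few raters and a factor that differs mainly between clinicians, and no section states such a link. When the factor is unrelated to clinician the error rate stays near 5%, and when it is balanced within clinician the test is conservative.

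Finally, only one of three questionnaire versions is affected. The organizational models also draw on other indicators, efficacy data, interviews and Focus Groups, and device contrasts are observational whatever error term is used. This limits the weight of the point but does not remove it.

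**Conclusion.** The point holds in a conditional form and for the clinician version only. Repeat rating is very probable, the named methods do not allow for it in their ordinary form, and the resulting error rates can be wrong in either direction. Over ICC 0.05 to 0.3 and 6 to 24 clinicians, type I error at a nominal 5% is about 7% to 43% with the factor constant within clinician and 6% to 24% with an 80/20 split. It is about 5% with the factor unrelated to clinician, and falls to 2% with it balanced within clinician. The number of clinicians, the ICC and the spread of devices and diagnoses over clinicians are all assumptions, so no single figure can be given, and even the direction is open. This is a cheap improvement to the stated method, not evidence that the planned results would be invalid.

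**What to change.** State in section 2.7 that scores from the clinician-completed questionnaires will be analysed with a mixed model that has a random intercept for clinician, using the rater identity the form already collects, and Satterthwaite or Kenward-Roger degrees of freedom. Analyse the patient and parent versions separately; they do not need this term. Report the number of clinicians and the number of patients each rated.

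The cost is one or two sentences and a mixed-model run in SPSS, the software already planned, with no new data. The downside is wider intervals for factors that vary mainly between clinicians, which reflects how little information those comparisons hold.

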## Abstract

**Background/Objectives:** In recent years, the advent of new technologies has fostered their application in neuro-psychomotor and language rehabilitation, particularly since the COVID-19 pandemic. Tele-rehabilitation has emerged as an innovative and timely solution, enabling personalized interventions monitored by clinicians. TABLET TOSCANA project aims to develop innovative tele-rehabilitation organizational models in children, adolescents and young adults with congenital and acquired developmental disabilities, using the Virtual Reality Rehabilitation System (VRRS) Home Kit and the MedicoAmico APP. **Methods:** The trial is designed according to the CONSORT statement guidelines. The project encompasses three phases: adapting the technologies for pediatric use, validating them through a wait-list study, and analyzing feasibility and effectiveness data to define new organizational models. A randomized wait-list-control study with 100 subjects aged 6 to 30 years will compare tele-rehabilitation versus prosecution of standard care. **Discussion:** Although literature highlights tele-rehabilitation benefits such as improved access, cost savings, and enhanced treatment adherence, practical implementation remains limited (i.e., the definition of standardized procedures). TABLET TOSCANA project seeks to address these gaps by focusing on multi-domain treatments for neurodevelopmental disabilities and emphasizing the integration of tele-rehabilitation into local health services. **Conclusion:** The project aims to improve the continuity and intensity of care through innovative models that integrate tele-rehabilitation into local health services. The results could inform healthcare policies and promote the development of innovative and collaborative models of care, paving the way for more effective and widespread tele-rehabilitation solutions and fostering collaborative networks among professionals.

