Within this framework, TABLET TOSCANA aims to develop innovative organizational models that foster the continuity of care through tele-rehabilitation for neuro-psychomotor and language functions using Khymeia technological devices in subjects with congenital and acquired developmental disabilities. Particularly, organizational dimensions, acceptability, the usability of proposed solutions, and the performance of the involved ICT, unrelated to the effectiveness of tele-rehabilitation, will be assessed as the primary objective of the study, differently from traditional literature. In addition, the secondary objective will be to evaluate the clinical effectiveness of the tele-rehabilitation intervention. We hypothesize that the TABLET TOSCANA project could establish a new organizational model to be implemented at the territorial level and integrated into routine clinical practice, improving the taking charge of the rehabilitation services for children with neurodevelopmental disabilities.

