### 2.3. Sample Size

Based on the annual count of children referred to the recruiting centers for clinical management and rehabilitation, a final sample of 100 subjects is deemed sufficient for conducting a *t*-test to analyze differences in primary endpoints between groups, assuming an effect size (d) of at least 0.4, a significance level (α) of 0.05, and a power (1-β) of 0.8.

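### Section 2.7 bases efficacy on pre–post differences and names no between-arm contrast for any clinical outcome, although the trial is randomised against standard care

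*Protocol article*

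**What the plan says.** The abstract describes a randomised wait-list-control study of 100 subjects that "will compare tele-rehabilitation versus prosecution of standard care". Section 2.1.2 gives the measurement schedule: "All subjects will be evaluated before (T0) and after (T1) the 3-month intervention period (tele-rehabilitation or traditional rehabilitation"). The WG has one further assessment, T1 plus, after its own three months of tele-rehabilitation. The Introduction states that "the secondary objective will be to evaluate the clinical effectiveness of the tele-rehabilitation intervention"; the primary objective is organisational dimensions, acceptability, usability and performance of the technology.

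On how efficacy will be obtained, section 2.7 says that "inferential analyses will be carried out to assess pre–post-treatment differences, gain efficacy data", and adds only that the different devices will also be considered. Section 2.1.3 says that "efficacy data acquired from pre–post-intervention cognitive, motor, and language assessments will be considered".

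Arms are compared in two other places. Section 2.7 speaks of "analyzing potential baseline differences between groups explored and computing the p values", which concerns baseline only. Section 2.3 plans a t-test "to analyze differences in primary endpoints between groups", which concerns the primary endpoints. The ANOVA or regression factors in section 2.7 are age, diagnosis, functional profile and device. Randomised arm is not listed.

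**The concern.** The article names a quantity for efficacy, and that quantity is not the one the design was built to estimate. Eighty of the 100 participants are children. They are re-tested after three months on performance measures such as digit span, Corsi blocks, reading, balance and walking distance (section 2.6.2). Scores can rise over that interval through development, familiarity with the test, regression to the mean and whatever other care continues. A test of T1 against T0 inside one arm cannot separate these from an effect of tele-rehabilitation. The randomised wait-list arm can.

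If the sentence is followed as a within-arm test, a significant change could be reported as efficacy even where standard care produced the same change. Section 2.6.2 says the clinical data will be merged with the primary outcomes to shape the new organisational models, and section 2.1.3 intends those models for regional health planning. The result would therefore be used.

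**Working it through.** **1. Where the arms are compared.**

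| Place | What is compared | Between arms? |
|---|---|---|
| Abstract | Tele-rehabilitation and standard care | Yes, no outcome named |
| 2.3 | Primary endpoints, t-test | Yes |
| 2.7, first sentence | Baseline characteristics | Yes, at T0 only |
| 2.7, ANOVA/regression | Age, diagnosis, functional profile, device | Arm not listed |
| 2.7, efficacy sentence | Pre–post differences, device | Arm not named |
| 2.1.3 | Pre–post assessments | Arm not named |

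No row links the clinical outcomes to the randomised contrast, although section 2.1.2 supplies T0 and T1 in both arms.

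**2. The plan's own figure.** The only number attached to a group comparison is in section 2.3: "a final sample of 100 subjects is deemed sufficient" for a t-test with d = 0.4, α = 0.05 and power 0.8. A two-sided two-sample t-test on those inputs needs 99 per arm, 198 in total; 50 per arm gives 51% power. So 100 is not reproduced as a between-group total. That is a separate matter about the primary endpoints and does not decide this point.

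**3. What a within-arm test does when treatment has no effect.** Inputs:
- Full arm n = 50, from 100 subjects randomised 1:1.
- n = 20, an illustrative assumption, because section 2.6.2 selects tests to suit each patient and not everyone takes every test.
- Gain g from T0 to T1 that would occur in either arm, in SD units: 0.1, 0.2 or 0.3 (assumed).
- T0–T1 correlation r: 0.5 or 0.7 (assumed), with equal SD at both times.
- Two-sided α = 0.05.

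The SD of a change is √(2(1 − r)), so the standardised mean change is dz = g/√(2(1 − r)). For g = 0.2:
- r = 0.5: dz = 0.2/√1.0 = 0.200
- r = 0.7: dz = 0.2/√0.6 = 0.258

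The rejection rate is the power of a paired t-test at that dz (noncentral t, n − 1 degrees of freedom):

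| g | n = 50, r = 0.5 | n = 50, r = 0.7 | n = 20, r = 0.5 | n = 20, r = 0.7 |
|---|---|---|---|---|
| 0.1 | 11% | 15% | 7% | 8% |
| 0.2 | 28% | 43% | 14% | 19% |
| 0.3 | 55% | 77% | 25% | 38% |

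A between-arm test has a 5% rejection rate in every cell, because the common gain cancels.

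**4. What the between-arm analysis can detect.** With 50 per arm all taking the same test, the unadjusted t-test detects d = 0.566 with 80% power. Adjusting for T0 multiplies the residual SD by √(1 − r²):
- r = 0.5: 0.566 × 0.866 = 0.49; power at d = 0.4 is 63%
- r = 0.7: 0.566 × 0.714 = 0.40; power at d = 0.4 is 79%

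The controlled analysis is therefore usable. Tests taken by fewer participants will detect only larger effects.

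**The case against.** The strongest reply is that nothing in the article says the control arm is set aside. Section 2.1.2 uses before and after for a period that is either tele-rehabilitation or traditional rehabilitation, so pre–post differences may well mean T0–T1 changes compared between arms, as the abstract implies. That stands. A reader might infer that the plan discards its randomised control. That is a natural reading of the efficacy sentence but not the only one, and the documents do not establish it.

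A reader might also suppose that the EG's T0–T1 change and the WG's T1 to T1 plus change will be pooled into one pre–post test of 100. No such analysis is described, so no figure for it is given here.

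Model detail is commonly left to a full protocol or analysis plan that is not shown. That stands for covariates and missing data. It does not cover a sentence that positively names pre–post differences as the source of efficacy, next to a list of factors from which arm is absent.

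The illustrated rates rest on values the documents do not give, and per-patient test selection makes a full arm of 50 on one test unlikely; hence the n = 20 columns. Section 2.6.2 chooses tests with normative data. Age-normed scores could absorb part of development, but not practice effects, regression to the mean or other care, and the article does not say normed scores will be analysed.

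The baseline p values bias no efficacy estimate and are a minor matter.

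**Conclusion.** The concern holds as a defect of wording with real consequences. Sections 2.7 and 2.1.3 name pre–post differences as the basis for efficacy, and no EG–WG contrast is stated for any clinical outcome, in a trial whose abstract promises that comparison and whose schedule makes it available. The wording permits an uncontrolled test.

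If that test were used with no treatment effect and a 0.2 SD common gain, it would be significant 28–43% of the time at n = 50 and 14–19% at n = 20, for r between 0.5 and 0.7. These figures show the direction and order of the error. They do not forecast it: the gain, the correlation and the smaller n are assumed, and the excess is small at 0.1 SD with 20 participants.

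The severity is should-fix, since clinical effectiveness is the secondary objective and the primary one does not depend on it.

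**What to change.** Replace the efficacy sentence in section 2.7, and align section 2.1.3 with it:

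*For each clinical outcome, efficacy is estimated as the EG minus WG difference at T1, from a linear model adjusted for the T0 value of the same test and, as far as the number assessed allows, the stratification factors, among randomised participants assigned that test at T0, analysed as allocated, with 95% CI. Within-arm pre–post changes, including WG T1 to T1 plus, are descriptive or supportive only.*

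The population is limited to those assigned the test at T0 because tests are chosen per patient and no single test need be available in everyone randomised. Restricting on a choice made at T0 keeps the comparison randomised only if the choice precedes allocation, so the text should say that it does. A comparison of T0–T1 change between arms would also use the control; the T0-adjusted model is suggested for its precision.

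The cost is wording. T0 and T1 are already collected in both arms. The one drawback is that sparsely used tests will support fewer covariates. The baseline p values can be dropped at the same time, with T0 and the stratification factors as the covariates fixed in advance.
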